## Methods

### Study setting and design

In Tanzania, 1,500,000 people are living with HIV infection and 399,886 are on ART [36]. The Global Hunger Index is 17.3, indicating serious levels of hunger [37]. The study is conducted in Shinyanga Region, a resource-poor region in the northwest “Lake Zone” of Tanzania where approximately 17 % of households have poor or borderline food consumption and HIV prevalence is 7.4 %, making this an ideal setting to examine how food and cash assistance may influence adherence to ART [38, 39].

We designed a 3-arm parallel group randomized trial to examine the effectiveness of short-term food and cash assistance added to the standard of care HIV services, including nutrition assessment and counseling (NAC). We include a standard-of-care comparison group that does not receive food or cash transfers. Participants will be recruited from 3 facilities,^1^ randomized to one of three study arms, and followed for 12 months: during the 6 month intervention period and then for another 6 months post-intervention. All sites participating in the study are currently trained in and implementing the President’s Emergency Plan for AIDS Relief (PEPFAR) Nutrition Assessment, Counseling, and Support (NACS) program [40].

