### Randomization

Participants are randomized into the food, cash, and comparison arms in a 3:3:1 ratio, stratified by site, using random permuted block sizes of 7, 14, and 21. Randomization procedures were conducted at the University of California, Berkeley and the procedures and group assignments were inaccessible to the local research team. Randomization assignments were listed in opaque sealed envelopes that were sequentially numbered. After participants provided written informed consent, trained research staff at study clinics selected the next envelope in numeric order and broke the seal to reveal the randomization assignment. Due to logistical considerations, participants and investigators were not blinded to intervention assignments.

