### Data collection

A comprehensive in-person interview about individual and household characteristics, food security, ART adherence, and health service utilization will be conducted at baseline, 6 and 12 months along with quantification of plasma viral load. Visit attendance, CD4 count, pharmacy pick-up data, and other clinical and prognostic markers will be abstracted from medical and pharmacy records at 0, 6, and 12 months.

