### Secondary outcomes

Retention in care will be measured by abstracting all scheduled and unscheduled visits from the medical record. We will use these dates to compute retention in care in several ways, following Mugavero et al.’s recommendations about how to define and measure retention in care in the absence of a gold standard [49]. We will first determine “appointment adherence,” the proportion of scheduled visits that are completed during the 0–6 and 6–12 month observation periods. We will also compute the number of “missed visits,” to facilitate comparisons to previous studies, and parameterize this indicator both as a binary and continuous variable for the analysis.Change in food security, as measured by the validated Household Hunger Scale [42] and the Household Dietary Diversity Score [50].Change in BMI, computed as body weight in kilograms (kg) divided by height in meters squared;Weight gain (kg); andViral suppression, measured as the proportion of participants with viral load <400 copies/mL at 6 and 12 months;Self-reported ART adherence, measured with a visual analog scale [51] and defined as the proportion of patients who reported taking all of their prescribed doses in the previous 5 days, averaging across all drugs in the patient's regimen, at 6 and 12 months;Participation in the labor force, including whether the participant is currently working and the number of days the participant was unable to work during the study because of illness or disability.

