### Analysis plan

We will first conduct a modified intent-to-treat analysis including participants with at least one post-enrollment visit. We will express the relationship between treatment arm (NAC, NAC plus food assistance, and NAC plus cash transfer) and MPR ≥95 % as risk differences with 95 % confidence intervals (CI). CIs will be adjusted for multiple comparisons between the three treatment groups using Bonferroni’s adjustment and the *pwcompare* compare command in Stata 14 (College Station, Texas).

To assess Objective 1, we will compare the proportion of individuals with MPR ≥95 % among those receiving NAC plus food to those receiving NAC plus cash transfers at 6 months. Only Objective 1 will be assessed in terms of non-inferiority; all other comparisons will be tests for superiority. The proportion of participants with MPR ≥95 % in both groups and the associated two-sided 95 % CI for the difference will be estimated. Non-inferiority of NAC plus cash transfers will be defined as the lower 95 % CI of the between-group difference in the primary outcome lying above a threshold of −10 % [55, 56]. If non-inferiority is evident, we will then assess whether NAC plus cash transfers is superior to NAC plus food transfers using a Wald test with alpha = 0.05.

To assess Objective 2, if the NAC plus food and cash transfer groups are not statistically different from each other based on examination of 95 % confidence intervals, we will pool the groups together and create a binary explanatory variable indicating NAC alone or NAC plus cash or food. We will then examine the effect of receiving NAC plus food or cash assistance on ART adherence compared to NAC alone.

We will potentially conduct two secondary analyses. First, if the randomization scheme produces imbalanced baseline characteristics among study participants in each of the three groups, these covariates will be included in regression models to generate adjusted risk differences and 95 % CIs. In addition, we will conduct a per protocol analysis using data from participants who received at least a minimum exposure to the interventions and for whom MPR was available at 6 months. Thus, we will construct a regression model with the 3-level treatment group and restrict the intervention groups to individuals who received ≥1 food basket or cash transfer during the 6-month intervention period.

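### Site stratifies the randomisation but is not named in the primary analysis, and the only stated covariate adjustment is chosen by observed baseline imbalance

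*Protocol article*

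**What the plan says.** The protocol article's Randomization section states: "Participants are randomized into the food, cash, and comparison arms in a 3:3:1 ratio, stratified by site, using random permuted block sizes of 7, 14," with 21 as the third block size. Study setting and design gives the number of strata: "Participants will be recruited from 3 facilities". The Randomization section also says that neither participants nor investigators were blinded.

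The Analysis plan relates arm to MPR ≥95% "as risk differences with 95 % confidence intervals (CI". It names no site term and no baseline covariate for this analysis. Adjustment appears only under the sentence "We will potentially conduct two secondary analyses", the first of which is conditional: "if the randomization scheme produces imbalanced baseline characteristics among study participants in each of the three groups, these covariates will be included" in regression models that yield adjusted risk differences. No criterion for imbalance and no list of candidate covariates is given.

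Baseline information is plentiful. Data collection says: "A comprehensive in-person interview about individual and household characteristics, food security, ART adherence, and health service utilization will be conducted at baseline", with plasma viral load measured at the same time and CD4 count and other prognostic markers abstracted from records at month 0.

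**The concern.** Three things go together.

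- **The stratifier is missing from the stated analysis.** Stratified blocks remove between-site variation from the arm comparison. A standard error that ignores site still counts that variation, so the interval is wider than it needs to be whenever site predicts adherence.
- **The adjustment rule selects on the wrong property.** Under sound randomisation, imbalance arises by chance. A covariate is worth adjusting for when it predicts the outcome, whether or not it is imbalanced. Because blocking keeps site balanced, an imbalance trigger will rarely select the one variable that the design itself marks out.
- **The adjusted model is not fixed beforehand.** With no criterion and no list, its content depends on the observed data, and investigators know the allocations.

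At stake is some precision in a trial planned at 80% power without reserve, and the credibility of the adjusted result if it differs from the unadjusted one. Validity of the primary comparison is not at stake.

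**Working it through.** **Inputs from the article (Sample size and power):** 75% with MPR ≥95% in the food arm, with the same rate in the cash arm under the alternative; margin 10 points; one-sided alpha 0.025; 80% power.

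**Reproducing the plan's figure.** n = (1.96 + 0.8416)² × 2 × 0.75 × 0.25 / 0.10² = 294.3, so 295 per arm, as stated. The formula contains no site or covariate term.

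**Unadjusted interval.** SE₀ = √(2 × 0.1875 / 295) = 0.03565; half-width 1.96 × SE₀ = 6.99 points.

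**Site-adjusted interval.** The article gives no rates by site. I assume three equal sites averaging 75% and vary the spread. With W the mean of p(1−p) over sites, the variance ratio is W / 0.1875, SE₁ = SE₀ × √(W / 0.1875), and the excess width of the unadjusted interval is SE₀/SE₁ − 1.

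Example, 65/75/85%: W = (0.2275 + 0.1875 + 0.1275)/3 = 0.1808; ratio 0.964; excess 1/√0.964 − 1 = 1.8%.

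Non-inferiority power when the arms are truly equal is Φ(0.10/SE₁ − 1.96) with site in the model, and Φ((0.10 − 1.96 SE₀)/SE₁) when site is ignored.

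| Assumed site rates (%) | Variance ratio | Excess width, unadjusted | Half-width with site (points) | Power, site ignored | Power, site included |
|---|---|---|---|---|---|
| 75/75/75 | 1.000 | 0% | 6.99 | 80.1% | 80.1% |
| 70/75/80 | 0.991 | 0.5% | 6.96 | 80.2% | 80.4% |
| 65/75/85 | 0.964 | 1.8% | 6.86 | 80.5% | 81.5% |
| 60/75/90 | 0.920 | 4.3% | 6.70 | 81.1% | 83.3% |
| 55/75/95 (extreme) | 0.858 | 8.0% | 6.47 | 81.9% | 85.7% |

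**Simulation check.** I simulated site-stratified permuted blocks of 7, 14 and 21 at 3:3:1, with 229 participants per site over all arms (about 229 × 3/7 = 98 per transfer arm per site) and 6,000 trials per setting, for the first four rows. Coverage of the unadjusted 95% interval lay between 0.944 and 0.958. With a true difference of −10 points, the unadjusted analysis declared non-inferiority in 2.0% to 2.7% of trials. The simulation error there is about √(0.025 × 0.975/6000) = 0.2 points, so there is no sign of inflation above 2.5%.

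**Prognostic baselines.** If a fixed set explained a share R² of the outcome variance, SE = SE₀ × √(1 − R²). At R² of 5% and 10%, power at 295 per arm would be about 82% and 84%. The article gives no R², so these values are illustrative.

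**How often an imbalance trigger fires.** If each of k independent baseline characteristics were tested at 5% (an assumption, since no criterion is stated), the chance that at least one is flagged is 1 − 0.95^k: 40% for k = 10 and 64% for k = 20.

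**The case against.** The best defence is that this is a condensed article. Not naming site does not exclude it, the non-inferiority decision rests on a prespecified interval, and the gain is small. Much of that stands, and it rules out several stronger readings that a reader might infer.

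- **That site can never enter the model.** Not so. Incomplete blocks, or dropping participants without a post-enrolment visit from the modified intent-to-treat set, could unbalance site, and nothing forbids a site term. It is unlikely to be selected, not barred.
- **That the intervals are too wide as a matter of fact.** This depends on site differences that the article does not report. If sites are alike, the excess is zero.
- **That the primary result is data-dependent or its error rate inflated.** The imbalance rule governs only a potential secondary analysis. The unadjusted comparison errs, if at all, towards caution.
- **That the change outcomes are wrongly analysed.** The article lists endpoints such as "Change in food security, as measured by the validated Household Hunger Scale" but states no model for them, and calling an endpoint a change does not rule out adjustment for baseline. Nor can a gain be quantified. With r the baseline–follow-up correlation and k the ratio of baseline to follow-up SD, the variance of the baseline-adjusted estimate relative to the change-score estimate is (1 − r²)/(1 + k² − 2rk). At r = 0.5 the saving is 25% for k = 1, 5% for k = 0.7 and 0% for k = 0.5. Enrolment requires a hunger score of at least 2, which restricts the baseline spread and makes k = 1 doubtful for that score. Neither r nor k is given.

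The defence does not cover the adjustment rule, which the article states outright. An analysis plan that used a fixed covariate set would depart from it.

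**Conclusion.** The point holds as a modest matter of precision and prespecification. Randomisation is stratified by site, the stated primary analysis names no site term, and the one stated adjustment rule selects covariates by chance imbalance after the data are seen.

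For site spreads up to 30 points, ignoring site widens the interval by 0% to about 4% and forgoes 0 to about 2 points of non-inferiority power. These figures assume three equal sites averaging 75% and 295 evaluable per arm. Prespecified prognostic baselines might bring more, by an amount the article does not allow one to estimate. The unadjusted risk difference remains valid.

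There is little power to spare: 339 per arm less 15% leaves 288, and Φ(0.10/√(0.375/288) − 1.96) is about 79%.

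**What to change.** 1. State that the primary risk difference for MPR ≥95% accounts for site, either as a site-stratified risk difference or as a standardised one from a regression with site indicators. Both keep the effect on the scale of the −10 point threshold.
2. Delete the imbalance trigger. Name a short list of prognostic baselines already collected, for example baseline viral load and CD4 count, and use it for the adjusted analysis whatever the observed balance.
3. As a recommendation only, adjust the change outcomes (Household Hunger Scale, dietary diversity, BMI, weight) for their baseline value and site.

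The cost is analysis-plan wording, plus a rule for missing baseline values, since CD4 count comes from record abstraction. No new data or participants are needed. The wording should be fixed before outcomes are compared by arm.

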
#### Conditionality

Participants in the food or cash assistance arms of the study are eligible to receive transfers for up to the first 6 consecutive months of the study, conditional on attending their scheduled visit with their HIV care provider. Trained research assistants consult the medical record to verify visit attendance. (In rare instances when visits are scheduled 60 or 90 days apart by the provider, participants receive the total value of 2 or 3 monthly transfers, respectively, if they attend the scheduled visit). After a detailed review of scheduling patterns, we developed a decision rule for eligible visits: transfers can only be made once every 26 days (to ensure that no one receives a transfer more than once every 4 weeks), and the actual visit must occur within a 4 day window (+/− 4 days) from the scheduled visit to encourage adherence to the physician’s recommended monitoring plan.

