### Primary outcome

The primary outcome is ART adherence at 6 months, measured with the medication possession ratio (MPR), the proportion of time an individual is in possession of >1 ART dose or prescription for ART [44]. MPR is computed from pharmacy dispensing records as the number of days ARVs are prescribed or dispensed divided by the number of days in the interval, and has been shown to be associated with short-term virologic outcomes [44–47]. We will determine the proportion of patients with MPR ≥95 % (the 95 % cutpoint is based on prior studies [48]) during the 0–6 month interval (primary outcome).

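### The secondary per-protocol analysis requires an earned transfer in the food and cash arms but has no matching condition for NAC, so its contrasts with NAC favour transfers if those who never earn one adhere less well

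*Protocol article*

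**What the plan says.** The Analysis plan puts first a "modified intent-to-treat analysis including participants with at least one post-enrollment visit", one rule for all three arms. It then says "We will potentially conduct two secondary analyses", the second being per protocol. That set takes participants with a minimum exposure "and for whom MPR was available at 6 months". The model will "construct a regression model with the 3-level treatment group and restrict the intervention groups to individuals who received" at least one food basket or cash transfer in the 6-month intervention period. The treatment variable keeps its three levels, so NAC remains the comparator, and no exposure or attendance condition is stated for it.

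Under Conditionality, a transfer is "conditional on attending their scheduled visit with their HIV care provider", and "the actual visit must occur within a 4 day window" either side of the scheduled date. Under Primary outcome, "MPR is computed from pharmacy dispensing records as the number of days ARVs are prescribed or dispensed", over the 0–6 month interval.

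**The concern.** Having received a transfer is not a baseline characteristic. It records that the participant kept at least one scheduled visit close to its date after randomisation, in the same months over which MPR is computed. A food or cash participant who disengages, or who always attends outside the window, leaves the per-protocol set. A NAC participant who behaves identically stays in, provided an MPR can be computed. If such people adhere less well than others, the two transfer arms lose poor adherers that NAC keeps.

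At stake is a secondary result that readers would naturally take as support for Objective 2 (transfers better than NAC alone). Part of any per-protocol advantage over NAC could come from the selection rule rather than from food or cash.

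**Working it through.** **Planning figures used as the yardstick.** Sample size and power gives 60 % with MPR ≥95 % in NAC, 75 % in the combined transfer arms (15 points), alpha 0.05, 15 % loss and a NAC group of 110. With allocation of 6:1 pooled ("Participants are randomized into the food, cash, and comparison arms in a 3:3:1 ratio"), a two-sided test, 80 % power (printed for Objective 1 only, assumed here) and a continuity correction, the requirement is 93 in NAC. Then 93/0.85 = 109.4, rounded up to 110, which matches. The total also matches: 2 × 339 + 110 = 788.

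**Inputs the article does not give (assumed).**
- f: the share of participants, among those with an MPR, who would never earn a transfer
- q: their rate of MPR ≥95 %

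**Formula.** Let p be the rate in every arm when there is no treatment effect, and r the rate among those who would earn a transfer. Then p = (1 − f)r + fq, so r = (p − fq)/(1 − f). The filtered transfer arms show r and NAC shows p, so

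bias = r − p = f(p − q)/(1 − f).

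**Results with p = 0.60**, in percentage points favouring transfers:

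| q | f = 2 % | f = 5 % | f = 10 % | f = 15 % |
|---|---|---|---|---|
| 0 | +1.2 | +3.2 | +6.7 | +10.6 |
| 20 % | +0.8 | +2.1 | +4.4 | +7.1 |
| 40 % | +0.4 | +1.1 | +2.2 | +3.5 |
| 60 % | 0 | 0 | 0 | 0 |

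Examples: 0.05 × 0.40/0.95 = 0.021; 0.05 × 0.60/0.95 = 0.032; 0.15 × 0.60/0.85 = 0.106.

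**Effect on a test.** After 15 % loss, NAC has 110 × 0.85 ≈ 94 and the pooled transfer arms 678 × 0.85 ≈ 576, reduced to 576(1 − f) by the filter. For f = 10 % and q = 0, the rates are 66.7 % of 518 against 60 % of 94. The standard error is √(0.667 × 0.333/518 + 0.60 × 0.40/94) = 0.0546, and 0.0667/0.0546 = 1.22. The chance of a significant result favouring transfers is P(Z > 1.96 − 1.22) ≈ 23 %, against a nominal 2.5 %. Other settings:

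| q | f = 2 % | f = 5 % | f = 10 % | f = 15 % |
|---|---|---|---|---|
| 0 | 4.1 % | 8.4 % | 23 % | 49 % |
| 20 % | 3.5 % | 5.8 % | 13 % | 25 % |

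Simulation with 20,000 trials per setting agrees to within 1 percentage point. These rates are for the pooled contrast without Bonferroni adjustment. Single-arm rejection rates would differ, but the bias in points is the same for each arm under these assumptions.

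**Same rule in all arms.** When the attendance condition is also applied to NAC, the simulated mean difference is within 0.1 points of zero and the favourable rejection rate is 2.0–2.4 %. This holds only if transfers do not change attendance.

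**The case against.** The strongest reply is that little hangs on this analysis and that the bias may be small. Much of that stands.

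- **It is secondary.** The modified intent-to-treat analysis comes first with one rule for all arms, and no decision rule uses the per-protocol result. This limits the consequence but does not make the per-protocol contrast with NAC sound.
- **The bar is low.** Visits are typically monthly, so one on-time visit in six months should exclude few people. Nothing in the article supports a share as high as 15 %.
- **Those excluded need not all fail.** The window is two-sided, so an early visit can also forfeit a transfer without a gap in supply. MPR ≥95 % over about 182 days allows about 9 uncovered days (0.05 × 182 = 9.1). Data collection lists visit attendance and pharmacy pick-up separately, so the tie between them is an inference. Setting q = 0 is therefore the extreme case.
- **NAC is not wholly unfiltered.** A reader might infer that it is, but the MPR-available condition covers every arm. Never-attenders without an MPR drop out of NAC too, which lowers f. It does not help with someone who attends only outside the window and still has an MPR.

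A reader might also infer that food and cash participants are selected differently, because cash goes by mobile money and food is a physical basket, and that the non-inferiority comparison is therefore compromised. The documents do not support this. Interventions says both are distributed on the same two days each month, the visit condition and the one-transfer filter are identical, and no shortfall in collection is reported. The Analysis plan does not present the per-protocol model as a check on non-inferiority.

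**Conclusion.** The point holds for the food–NAC and cash–NAC per-protocol contrasts only. The stated rule selects two arms on post-randomisation attendance and leaves the third without that condition. The direction is towards transfers, conditional on never-earners adhering less well than the rest; if they adhere equally well, there is no bias.

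The size cannot be fixed from the article. With 60 % in every arm and no true effect, a modest share of never-earners (2–5 %) gives +0.8 to +2.1 points at q = 20 % and +1.2 to +3.2 points at q = 0. The figure of +10.6 points needs both a 15 % share and complete failure among them, so it is an upper illustration and not an expectation. All of these shrink if never-attenders in NAC have no MPR. The primary modified intent-to-treat result is untouched.

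**What to change.** State in the Analysis plan that the subset with at least one transfer will not be used for contrasts with NAC. Report it descriptively or for food versus cash only, and rest all NAC contrasts on the modified intent-to-treat set.

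If a three-arm per-protocol model is kept, define membership by one attendance rule applied to all arms from the same medical records. An example is at least one scheduled visit attended within 4 days either side of its date in months 0–6, whether or not a transfer was due. Label that analysis exploratory: transfers may themselves change attendance, so a common rule reduces the asymmetry without giving an unbiased contrast with NAC.

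The cost is wording. Scheduled and unscheduled visits are already to be abstracted for the retention outcome. With the common rule, slightly fewer NAC participants would enter a secondary analysis.
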